### Randomization

After baseline data collection, we will stratify study facilities by district. Within each stratum, we will randomize the facilities to one of three arms: private feedback (intervention), social recognition reward (intervention), or no feedback (control) with a 1:1:1 allocation ratio. The principal investigator will conduct randomization using a random number generator in Stata version 14.2. Parents/guardians will be recruited from the health facilities that they visit and assigned that facility's intervention status. Healthcare providers will likewise be assigned the intervention status of the facility where they work. Participants will not be blinded to the allocation. It is possible that healthcare providers in the control group, or the private feedback group, will learn about the interventions provided in the other arms. This is however unlikely given the short duration of the study. If they do learn of the interventions in the other arms and this causes them to improve the care they provide, this could lead to a dilution of effect.

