### Analysis

The primary causal identification strategy for the intent to treat analysis will be a difference-in-differences (DID) analysis comparing change in outcomes in the intervention groups to changes in outcomes in the control group. DID analyses have the advantage of controlling for differences between the groups at baseline. We will use the following model:

$$\begin{array}{l} Y_{if}=\;\mu +\;\gamma \cdot Private_{if}+\lambda \cdot T_{if}+\;\delta \cdot (Private_{if}\cdot T_{if})\\ \;+\eta \cdot Reward_{if}+\nu \cdot (Reward_{if}\cdot T_{if})+\varepsilon_{if} \end{array}$$

Here, *Y*_*if*_ is the outcome for individual *i* in facility *f*, μ is the mean outcome among individuals in the control facilities at baseline, γ is the mean difference between individuals in the intervention groups and control group at baseline, λ is the effect of time (T is a post intervention indicator), and δ and η are the estimators of interest: the difference between the change in the private or reward intervention groups and the change in the control group, respectively. ε_*if*_ is the individual error clustered at the facility level. We will conduct a sensitivity analysis assessing endline differences only and one imputing missing data. Additional secondary analyses will use discrete choice data and free-list responses from the providers to assess their views on quality of care. These analyses will allow us to assess if providers are inattentive to patient experiences or if they do not think that they are important, and if this changes as a result of the intervention.

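### The text names η as the reward-arm effect, but in the printed model, and by the text's own verbal definition, that effect is ν, which is never defined

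*Protocol article*

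**What the plan says.** The Analysis section of the protocol article sets out the primary intention-to-treat analysis as a difference-in-differences, "comparing change in outcomes in the intervention groups to changes in outcomes in the control group". Written in short form, the model is

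Y = μ + γ·Private + λ·T + δ·(Private·T) + η·Reward + ν·(Reward·T) + ε,

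where "T is a post intervention indicator" and the errors are clustered by facility.

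The explanatory text makes three statements that matter here:

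- On the private arm's main effect: "γ is the mean difference between individuals in the intervention groups and control group at baseline".
- On the effects to be reported: "δ and η are the estimators of interest".
- On what those estimators mean: "the difference between the change in the private or reward intervention groups and the change in the control group, respectively".

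The symbol ν appears in the equation but nowhere in the text.

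**The concern.** Symbol and words in one sentence point to different quantities. By symbol, the reward effect is the coefficient of the reward indicator alone. By words, it is a difference between two changes over time, and only the coefficient of the reward-by-T interaction is that.

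The description of γ adds to the confusion. It is said to hold the baseline gap for both intervention groups, although in the equation it multiplies the private indicator only. With γ described this way, the reward arm appears to have no baseline term of its own, and η can be mistaken for an effect. Of the six coefficients, one is misdescribed (γ), one is wrongly named as an effect (η) and one is undefined (ν).

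What is at stake is the primary result of one of the two intervention arms. A second analyst should be able to identify that coefficient from the plan without having to choose between the symbol and the sentence.

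**Working it through.** **Inputs.** The model, the meaning of T and the verbal definition come from the Analysis section. The timing of allocation comes from the Randomization section: "After baseline data collection, we will stratify study facilities by district", and facilities are then randomized within district. From Sample size estimation come 25 facilities per arm, 15 individuals per facility, and the examples of 46% to 54% (communication of diagnosis) and 14% to 9% (disrespectful care). No numerical result in the plan has to be reproduced, since the question is which coefficient is the effect.

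**Step 1: expected cell means from the printed equation.**

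| Arm | Baseline (T = 0) | Endline (T = 1) | Change |
|---|---|---|---|
| Control | μ | μ + λ | λ |
| Private | μ + γ | μ + γ + λ + δ | λ + δ |
| Reward | μ + η | μ + η + λ + ν | λ + ν |

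**Step 2: match to the verbal definition.** Change in private minus change in control is (λ + δ) − λ = δ, so the private arm is labelled correctly. Change in reward minus change in control is (λ + ν) − λ = ν, and η cancels. The baseline gaps are γ for private minus control and η for reward minus control.

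**Step 3: what η would show.** The model is saturated in arm and time, so the least-squares estimate of η is the reward baseline mean minus the control baseline mean. No endline observation enters it. Allocation follows baseline data collection, so under randomization its expectation is 0 whatever the intervention does.

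**Step 4: worked example.** Take control at 46% in both rounds and reward at 46% then 54%. Then η = 46 − 46 = 0 and ν = (54 − 46) − (46 − 46) = 8 points. Now take control flat at 46% and reward at 51% in both rounds, that is, a chance gap of 5 points and no effect. Then η = 51 − 46 = 5 points and ν = 0.

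**Step 5: simulation check.** 75 facilities, 15 individuals per round, 400 runs, least squares with facility-clustered errors. Assumed: control rate 46%, no time trend, between-facility standard deviation 0.05.

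| True reward effect | Imposed baseline gap | Mean η | η rejected | Mean ν | ν rejected |
|---|---|---|---|---|---|
| 0 | 0 | 0.0003 | 7.5% | −0.001 | 5% |
| 0.08 | 0 | 0.0003 | 7.5% | 0.078 | 37% |
| 0.16 | 0 | 0.0003 | 7.5% | 0.158 | 86% |
| 0 | 0.05 | 0.049 | 25% | −0.001 | 4% |

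The first three rows agree exactly in the η columns because η does not use endline data. The rejection rates come from only 400 runs and the assumed values, and are illustrative.

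**Step 6: how large a chance gap η could show.** For disrespectful care at 14%, the variance is 0.14 × 0.86 = 0.1204 and each arm has 25 × 15 = 375 respondents per round. The article gives no intraclass correlation, so a range is assumed. With SE = √(2 × 0.1204 × (1 + 14·ICC) / 375):

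- ICC 0.01: √(2 × 0.1204 × 1.14 / 375) = 0.027
- ICC 0.05: √(2 × 0.1204 × 1.70 / 375) = 0.033
- ICC 0.10: √(2 × 0.1204 × 2.40 / 375) = 0.039

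The formula ignores the stratification by district.

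**The case against.** The strongest defence is that the intended analysis is clear from everything except one symbol. The clause after the named estimators defines the reward effect correctly in words. The section opens with a difference-in-differences intent and gives control of baseline differences as its reason, which cannot be squared with reporting a baseline difference as the effect. The sample size is computed for a difference-in-differences design. The parallel private-arm parameter is right. The equation contains the reward-by-T term, so fitting it as printed produces the correct estimate, and only the label is wrong. The planned sensitivity analysis of endline differences is also informative: in the model's terms it estimates η + ν, which has expectation ν under randomization.

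All of this stands, and it limits the consequence. A reader might infer that the reward comparison as planned carries no information about the intervention, or that its power equals the significance level. The documents do not support that. It would follow only if an analyst took the symbol over the verbal definition, the opening of the section and the structure of the model. Nor does Step 6 show frequent false claims. At ICC 0.05 a gap must reach about 1.96 × 3.3 = 6.5 points to be significant, and that happens by chance in about 5% of trials. The plural in the description of γ is loose wording about a nuisance term and by itself affects no result.

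What the defence does not remove is the contradiction. The statement sits in the primary analysis specification, the coefficient it names is wrong for one of the two intervention comparisons, and the right one is left undefined. This is something the article states wrongly. It is not a detail left to a fuller document.

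**Conclusion.** The Analysis section contradicts itself on the primary reward-arm estimator. The text names η, which is the reward-minus-control difference at baseline; its own verbal definition corresponds to ν. This follows from the printed equation and needs no assumption.

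The size of the consequence is conditional. If η were reported, the reward result would reflect only chance baseline imbalance: 0 in place of 8 points in the protocol's communication example with a flat control arm, with a standard error of roughly 2.7 to 3.9 points for disrespectful care over an assumed ICC of 0.01 to 0.10. If ν is reported, nothing is lost. The verbal definition and the stated design make a slip of η for ν by far the likelier explanation. The point is therefore a necessary correction of notation in the primary analysis. It is not evidence of a faulty choice of analysis.

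**What to change.** Reword the explanatory sentence so that:

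- δ and ν are named as the estimators of interest, for the private and the reward arm respectively;
- γ is defined as the private-minus-control difference at baseline;
- η is defined as the reward-minus-control difference at baseline.

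Use the same definitions in any statistical analysis plan, and confirm that the analysis code and results tables take the reward effect from the reward-by-T coefficient. The cost is one sentence of text and a check of the code. The design, the data collection and the sample size do not change.

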## Discussion and implications

The study will assess three causes of poor patient experience: normalization of poor quality, low attention to poor quality, and lack of accountability to the community. Private reports of data on patients' experiences serve to improve providers' awareness of problems by giving providers specific information on areas where patients feel they need improvement. Social recognition by way of public reporting of providers' success in delivering high quality care, incentivize providers to improve and hold them accountable to the communities they serve. This study will provide evidence for which mechanisms affect patient experience and how communities can be involved to improve quality.

If successful, the intervention will provide a method for improving patient experience during outpatient care for sick children. The study will also provide a validated tool for measuring patient experience that could be used in similar contexts, contributing to the body of knowledge on how to measure the quality of care and in particular on the principles to adhere to when measuring quality of care (38). After completion of the study and analysis of the results, we intend to thoroughly discuss the anticipated mechanism of effect, the evidence that supports or contradicts these mechanisms. We will discuss how these findings fit into the literature on both the measurement of patient experience, and the accountability of healthcare providers to delivering high quality interpersonal care.

We expect the study to inform the Ministry of Health, Community Development, Gender, Elderly and Children; Regional and Council Health Management Teams; as well as local NGOs on sustainable and efficient means of addressing gaps related to patient experience as contributors to quality care. The current Health Sector Strategic Plan IV 2015 –June 2020 (HSSP IV) includes plans to promote and strengthen relationships between communities and health facilities, including through empowerment and accountability of health facility governing committees (25). Tested models for achieving these goals are of great interest to policy makers, both in Tanzania and countries with similar gaps in quality of care.

### Limitations

There are several potential limitations to this study. First, it is possible that healthcare providers could ask patients to give a favorable report of their experience. While there is no incentive for providers to ask patients to misreport the care received in the control and private feedback arms, there is some concern that providers may ask patients to misreport their care in the reward arm. However, even in this arm the incentive is low, as there is no punishment for poor care and no comparison to other providers. We will ask respondents whether a healthcare provider spoke to them about giving a positive response to the survey. Second, it is possible that healthcare providers could drop out of the study, or leave the health facility and no longer be eligible, between baseline and endline. We will track healthcare providers to determine if they decline to participate in follow-up (drop out) or leave the health facility. Third, because we are not providing feedback to specific providers on their individual behavior, but rather to a group of providers on the aggregate behavior at the health facility, that healthcare providers will not feel that they as an individual need to change. However, it is also possible that they will try to influence their colleagues' behavior as well as their own. We will use the provider surveys to capture information on their own feelings toward patient experience to build a theory for how the intervention did, or did not, affect change. Finally, the results of this study may not be generalizable to different levels of health facilities (e.g., care provided at hospitals), different types of care (e.g., care provided to adults), or different contexts outside of rural Tanzania. This is a proof of concept study and if the intervention is successful in improving provider behavior, the concept will need to be studied in other contexts.

## Ethics and dissemination

This study was reviewed and approved by the ethics committees at the Harvard T. H. Chan School of Public Health in the United States and the National Institute for Medical Research in Tanzania prior to the start of data collection. Written or oral informed consent will be obtained by Swahili-speaking, Tanzanian research assistants from all participants prior to participating in the study, and participants will be reminded that they can withdraw at any time. All spontaneously reported adverse events and other unintended effects of the study will be collected, assessed, and managed by the principal investigator. Adverse events will be reported to the ethics committees. Any updates to the study will go through ethics committee approval and will be included in the PACTR.

We have a two-part dissemination strategy. After all data have been collected and the results have been analyzed, we will develop a policy report to be shared with all stakeholders, including the district, regional, and national ministries of health. We will also develop and submit academic manuscripts to peer-reviewed journals to share our results more widely with the academic, policy-making, and implementation communities.

## Availability of data and material

Data sharing is not applicable to this article as no datasets were generated or analysed during the current study. The final trial dataset will be accessible by the principal investigator and co-investigators. A minimal, de-identified dataset will be made more widely available within two years of study completion.
